#### Home

Participants with COPD that select to continue with endurance training in a home setting will be provided with a cycle ergometer (Smart ZBike, Zycle, Valencia, Spain) for unsupervised supramaximal HIIT or MICT. Alternatively, if a participant would like to continue at home but does not want to receive a cycle ergometer, they can continue with walking-based HIIT or MICT (HIIT-Walk or MICT-Walk). The HIIT-Walk and MICT-Walk build on the same principles as the supramaximal HIIT and MICT exercise performed on a cycle ergometer but are modified to be suitable during walking. See Tables 2 and 3 for details.

**Table 3 Tab3:** Description of Endurance Training (ET) in line with TIDieR and CERT guidelines

Variable	Supramaximal HIIT	MICT	HIIT-Walk	MICT-Walk
1. ET objective	The ET objective for all interventions is to improve peak VO_2_ on a CPET and exercise duration on a CWRT.			
2. Training device / type of exercise	Cycling on a stationary cycle ergometer (Smart Zbike, Zycle, Valencia, Spain)		Outdoor walking	
3. Supervision and delivery	First 12 weeks and outpatient last 21 months: Group of 4-5 individuals under the supervision of a trained instructor^a^, face-to-face delivery / Home or mix last 21 months: unsupervised cycling, individual, phone call delivery every two weeks		Unsupervised walking training, individual, phone call delivery every two weeks	
4. Setting	First 12 weeks: outpatient (local gym or rehab center) / Last 21 months: Home, outpatient (local gym or rehab center) or mix (local gym or rehab center + home)		Home	
5. Adjunct	First 12 weeks: none / Last 21 months: RT (see Table 4)		RT (see Table 4)	
6. Program duration	12 weeks + ≈ 21 months		≈ 21 months	
7. Frequency of sessions	Week 1-6: 2x/week / Week 7-12: 3x/week / Week 15 to 102: 2x/week		Week 15 to 102: 2x/week	
8. Exercise selection	10×6 sec intervals against an individualized intensity with 48 sec recovery^b^ between intervals (20s passive, 28s active) for 10 min	Continuous cycling against an individualized intensity for 20 min	10×10 sec intervals at an individualized maximal walking speed with 50 sec of active rest between intervals for 10 min	Continuous walking at an individualized intensity for 20 min
9. Warm-up / cool-down	5 min at 30% of MAP at 50-70 RPM^c^		5 min at a walking speed at Borg dyspnea <3	
10. Intensity	Start intensity of 60% of MPO_6_ with aim of increasing up to 80% of MPO_6_ in session 3.	Start intensity at 50% of MAP with aim of increasing up to 60% of MAP in session 3.	Start intensity at a walking speed as tolerated at Borg dyspnea 4-8 at the end of the last interval	Start intensity at a walking speed as tolerated at Borg dyspnea 4-6 at the end of the last minute
11. Exercise volume	Exercise volume will be evaluated by: duration (min:ss), training load in kilojoule (intensity × duration), duration at intensity above MAP (mm:ss)		Cannot be accurately calculated	
12. Velocity of muscle action	80-90 RPM	60-70 RPM	Self-determined walking speed at Borg dyspnea 4-8 and 4-6 for HIIT-Walk and MICT-Walk, resp.	
13. Rest periods between series / type of rest incl. intensity	20 sec passive, 28 sec active rest at 30% of MAP between intervals	N/A	50 sec of active rest at Borg dyspnea < 3	N/A
14. Rest / sequence between exercises	If ET and RT are performed on the same day, a minimum of 15 min rest between ET and RT, and ET is performed first			
15. Recovery	At least 48h rest between sessions			
16. Attendance (% of sessions) / Adherence^d^	Completion rate, attendance rate, and adherence to exercise duration and intensity will be obtained.			
17. Specificity	Variables 6-16 are designed to achieve the ET objective (Variable 1)			
18. Progressive overload	Progression/overload criteria are seen in Table 1- 2		Progression/overload criteria are seen in Table 2	
19. Variation	Non-linear block periodization			
20. Individuality	Designed to lower the ventilatory demand, based on BCST data to set intensity	Designed per ATS/ERS guidelines^9^, based on CPET data to set intensity	N/A	N/A

*CPET *cardiopulmonary exercise test,* CWRT *constant-workload test,* ET* endurance training, *ATS/ERS* American Thoracic Society/European Respiratory Society, *MICT* moderate intensity continuous training, *HIIT* high-intensity interval training, *MPO*_*6*_ maximal mean power output for six seconds, *N/A* Not applicable, *RPE* rating of perceived exertion, *RPM* revolutions per minute, *RT* resistance training

^a^The instructor education consists of written, oral and visual instructions on how to perform HIIT & MICT exercises, and instructors are qualified health professionals (e.g. physiotherapists, exercise physiologists)

^b^Since it takes approximately six seconds for the bike to apply the necessary breaking resistance to reach target intensity, each interval is programmed to last 12 seconds with a 48 second recovery between intervals

^c^For those that cannot complete a CPET test according to guidelines, the warm-up will initially consist of 3-min seated rest and 2-min active warm-up as described for variable 9

^d^For those performing HIIT, MICT, HIIT-Walk or MICT-Walk during phase 2, attendance/adherence will be collected from a self-reported diary and followed up in the standardized phone calls every 14 days

#### Outpatient

Participants with COPD that select to continue in an outpatient setting will perform HIIT and MICT training in the same manner as during the initial 12-week period, supervised in small groups of 4–8 participants (see Tables 2 and 3).

#### Mix

For participants with COPD that select to continue in a mixed setting, home-based sessions will be combined with one supervised outpatient exercise session every 2 weeks (replacing one of the home-based sessions during these weeks). For example, for 1 month, the participant will complete six unsupervised home-based sessions and two supervised outpatient sessions (see Tables 2 and 3).

#### Resistance training (RT)

Irrespective of the originally assigned group (supramaximal HIIT or MICT) and chosen setting, all participants will also perform a RT regime. The RT regime will consist of ten lower- and upper-body exercises designed following American College of Sports Medicine guidelines [49] and other relevant RT literature for increasing muscular strength, endurance, and power. The goal of the RT regime (strength, endurance, or power) will change monthly. See Table 4 and additional file 5, Figure S1-S3 for details of the RT regime.

**Table 4 Tab4:** Description of resistance training (RT) in line with TIDieR and CERT guidelines

Variable	Description
1. RT objective	The aims of the RT exercises are to improve limb muscle strength, power, and endurance
2. Training device and type of exercise	All exercises will be performed using the body weight of the participant and/or with elastic bands (Thera-Bands®, The Hygienic Corporation, Akron, OH, USA). The participants will be provided with the elastic bands. If performed in an outpatient setting, available RT equipment will be used. (Umeå: leg press, leg extension, chest press and lat pull-down machines, Nautilus, Core Health and Fitness LLC, Vancouver, WA, USA. Hasselt: lat pull-down and leg press machines, Enraf–Nonius B.V. Echt, The Netherlands). At both centres, Free-weight dumbbells, (Ziva, Raleigh, NC 27606, USA) will be used for elbow and shoulder flexion)
3. Provider & Location	Each session will be performed unsupervised in the home setting of the participant or in an outpatient setting (local gym or rehab centre) or in an outpatient setting (local gym or rehab centre). The RT is performed individually and delivered via a two-weekly phone call
4. Warm-up	No specific warm-up will be conducted before start of the RT
5. Muscle actions	Exercises will be performed using dynamic concentric/eccentric muscle actions
6. Exercise selection & order	An exercise battery of ten exercises will be available. The participants will be instructed to choose and perform four exercises in each exercise session within a two-week period. A sit-to-stand exercise should always be included (if performed in an outpatient setting a leg press or knee extension should always be included), but the participant should select three additional exercises each session. A pre-determined exercise order will be provided in the following order: sit to stand (m. quadriceps), calf raises (m. triceps surae), latissimus row (m. latissimus dorsi), chest press (m. pectoralis major, m. deltoid anterior), elbow flexion (m. biceps brachii), and shoulder flexion (m. deltoid anterior). If requested by the participant, additional exercises can be added or removed from the 10 exercises that are initially provided. However, the sit-to-stand exercise should always be included. See additional file 5 Figure S1-S3 for more information, including illustrations, start and end positions, and instructions for exercise executions
7. Intensity (loading)	For elastic band/equipment exercises, to achieve adequate loadings, the elastic band will be stretched/or weight added so that the participant can do between 8–12 repetitions (8–12 RM) for muscular strength and between 15–25 repetitions (15–25 RM) for muscular endurance. For muscle power, [50, 51] the same load as for muscular endurance will be used, but the participant will perform 8–12 repetitions. Thus, although performing 8–12 repetitions for power, it should not be at 8–12 RM load, the patient should be able to perform additional repetitions with ease and the focus is on speed of contraction (see variable 9). For body-weight exercises (sit to stand, calf raises), three different levels will be available (level 1, 2, 3). The start-level will be individualized based on an individuals’ muscle function and RT experience. If needed additional levels will be provided
8. Exercise volume	Two sets per exercise will be performed. We will not be able to calculate exercise volume accurately for home exercises. For outpatient exercises, exercise volume will be calculated as repetitions × load
9. Velocity of muscle action	All muscle strength and endurance exercises will be instructed to be performed using a moderate velocity (1:1 s in the concentric and eccentric phase respectively), for two sets per exercise. For muscle power, the exercises should be performed at a maximal individual speed for the concentric phase of the movement – and 2–3 s in the eccentric phase
10. Rest periods between sets	For muscle strength and endurance, we will use 1–2 min rest between sets, while a minimum of 3 min of rest between sets is used for muscle power
11. Rest periods / exercises	Rest periods between exercises will be 4 min
12. Recovery	At least 48 h rest between sessions
13. Cool down/ stretching	No specific cool-down will be applied
14. Frequency and program duration	Two times per week for ≈ 21 months
15. Adherence	Self-reported attendance and adherence to predefined number of exercises and sets will be obtained
16. Specificity	Variables 4–9 are designed in line with ACSM guidelines and previous research to achieve the RT objectives
17. Progressive overload	Progressive overload will be achieved by an individual progression of each exercise, i.e., for muscle strength (target 8-12 RM). If a participant could not do 8 repetitions, the resistance is too great, and the resistance is reduced. If the participant could do more than 12 repetitions, the exercise is too easy, and the participant should increase the resistance/weight or the level of the exercise. To increase the loading (weight) on the elastic band exercises, the participant is instructed to "shorten" the length of the elastic band by moving his/her grip closer to the origin of the elastic band. E.g., in the shoulder exercise by moving your grip further down on the elastic closer to your feet. To decrease the loading the participant should "lengthen" the elastic band by moving his/her grip further from the origin of the elastic band. To increase/decrease the difficulty of the sit to stand or the calf raise exercises you change the level (Level 1–2-3). If using equipment, the loading is increased with 2–10%. For muscular endurance, the same principles would be applied but the repetition zone would be 15-25RM instead of 8-12RM; For muscle power, the progression of loading used will follow the muscular endurance progression. Participants will be instructed to change between muscular strength, endurance, and power every month. Every two weeks, progression will be guided based on 1) if target repetition range is reached or not, and 2) perceived heaviness ratings [47]CR-10) of the 2nd set of every exercise from the last performed session in the previous two weeks
18. Periodization	No pre-planned periodization of program variables will be included
19. Tailoring	Tailoring of the resistance exercises will be dependent on whether the goal is to increase muscular strength, endurance, or power. See e.g., variable 7 for how the loading is altered depending on the goal

*ACSM* American College of Sports Medicine, *RM* repetition maximum, *RT* resistance training

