### Objectives

#### Primary objectives

The primary objectives are as follows:To determine and compare the effect of 12 weeks of supramaximal HIIT and MICT on cognitive function, cardiorespiratory fitness, and quadriceps power in people with COPD compared to matched healthy controls (phase 1);To determine and compare the effect of 24 months of supramaximal HIIT, MICT, and usual care on cognitive function, cardiorespiratory fitness, and quadriceps power in people with COPD (phase 2).

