#### Passive control group: usual care

The passive control group will receive usual care alone and a standardized phone call (see additional file 4) every 3 months including assessment of symptoms of exacerbations. Health status (CAT) and disease-specific quality of life (CRQ) will be assessed by sending a letter with the questionnaires via the post for self-administration or by a phone call. We will match the participants in the usual care group to those randomized to HIIT or MICT by age, sex, disease severity (GOLD A/B/E), educational level, and physical activity.

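### The Phase 2 contrasts with usual care estimate endurance plus resistance training, so they cannot be attributed to HIIT or MICT alone

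*Protocol article*

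**What the plan says.** Under Primary objectives, the Phase 2 aim, for participants with COPD, is "To determine and compare the effect of 24 months of supramaximal HIIT, MICT, and usual care on cognitive function, cardiorespiratory fitness, and quadriceps power". Background and rationale likewise describes Phase 2 as exercise training, glossed as HIIT or MICT, set against usual care. Neither passage names resistance training.

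The intervention sections add it:

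- Resistance training (RT): "all participants will also perform a RT regime", whichever of the two exercise arms and whichever setting they are in.
- Table 4, frequency and duration: "Two times per week for ≈ 21 months".
- Table 4, objective: "The aims of the RT exercises are to improve limb muscle strength, power, and endurance".
- Table 3, adjunct row for the cycling arms: "First 12 weeks: none / Last 21 months: RT (see Table 4".

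For the third arm, Passive control group: usual care states: "The passive control group will receive usual care alone and a standardized phone call", the calls being three-monthly. Trial design says that this arm is outside the randomisation and is assessed at baseline and at 24 months. Statistical methods – outcomes specifies one three-arm model for Phase 2, and Maintenance program says that data are analysed by allocated arm under the labels supramaximal HIIT, MICT and usual care.

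**The concern.** The objective and the arm labels name one component of what the exercise arms receive; the intervention section prescribes two. Read as written, a 24-month difference from usual care would be reported as an effect of HIIT or of MICT, although the design offers no way to credit it to the endurance component.

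The stakes are highest for quadriceps power. Table 3 gives the endurance-training objective as peak oxygen uptake and constant-work-rate duration; muscle power is not in it. Table 4 gives power as one of the RT objectives. The Primary outcomes section treats the three primary outcomes as multiple rather than co-primary, so a result on any one of them can support an efficacy claim. A difference from usual care in quadriceps power alone could thus be presented as efficacy of HIIT or MICT.

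**Working it through.** **What each arm is prescribed, and when** (Tables 1 to 4; Trial design; Passive control group: usual care)

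| | HIIT | MICT | Usual care |
|---|---|---|---|
| Weeks 1–12, endurance | 30 sessions | 30 sessions | none |
| Weeks 1–12, RT | none | none | none |
| Weeks 15–102, endurance | 2 per week | 2 per week | none |
| Weeks 15–102, RT | 2 per week | 2 per week | none |
| Assessed at 12 weeks | yes | yes | no |
| Assessed at 24 months | yes | yes | yes |

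**Amount of RT.** Weeks 15 to 102 are 102 − 15 + 1 = 88 weeks, and 88 × 2 = 176 sessions. This takes the RT period of about 21 months to coincide with the endurance maintenance weeks in Table 2. Endurance sessions over 24 months are 30 + 176 = 206. RT is then 176 / (176 + 206) = 46% of prescribed sessions in each exercise arm.

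**What each contrast estimates.** Write E for the endurance effect of an arm, R for the RT effect and I for any interaction between them.

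- HIIT versus usual care, 24 months: E(HIIT) + R + I(HIIT).
- MICT versus usual care, 24 months: E(MICT) + R + I(MICT).
- HIIT versus MICT, 24 months: E(HIIT) − E(MICT), plus any difference in interaction. R cancels, so this is a modality effect on a common RT background.
- HIIT versus MICT, 12 weeks: E(HIIT) − E(MICT), with no RT in either arm.
- Either arm versus usual care, 12 weeks: not available, because usual care is not measured then.

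With no RT-only arm, no endurance-only arm after week 15 and no 12-week value in usual care, R cannot be removed from the first two lines by any choice of model.

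**Overlap with the outcome.** Table 4 requires a sit-to-stand in each session, or a leg press or knee extension in the outpatient setting. In power months it calls for maximal concentric speed. The primary test in the Quadriceps power section is a seated leg extension made with maximal speed and effort.

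**The plan's own figure for this outcome.** For a 19.4% difference, SD 26.8%, two-sided 0.05 and 80% power, n = 2 × (1.96 + 0.8416)² × (26.8 / 19.4)² = 29.96, or 30 per group. The plan states 30, so it is reproduced.

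**Illustration only.** The documents give no RT effect on quadriceps power, so a range is assumed. Set the endurance effect and interaction to zero and keep SD 26.8%. With 46 × 0.7 = 32 per arm after 30% drop-out, SE = 26.8 × √(2/32) = 6.70; with 46 per arm, SE = 26.8 × √(2/46) = 5.59. The two-sided chance of a significant contrast with usual care, by normal approximation, is:

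| Assumed RT effect | 32 per arm | 46 per arm |
|---|---|---|
| 0% | 5.0% | 5.0% |
| 5% | 11.6% | 14.6% |
| 10% | 32.0% | 43.2% |
| 15% | 61.0% | 76.6% |
| 19.4% | 82.5% | 93.5% |

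The table shows how the test would respond to RT, not how large the RT effect is. A larger sample makes the attribution problem no smaller.

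**The case against.** The strongest reply is that nothing is hidden. RT is listed as an adjunct in Table 3, has a table of its own, and its attendance and adherence are feasibility outcomes. HIIT and MICT can be read as arm labels, and comparing an exercise package with usual care is a legitimate design. On this view only the objective's wording lags behind the intervention, and estimand wording may properly come in the SAP.

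Much of that stands: the design is defensible and the remedy is wording. It does not make the point trivial. The objective states what the trial will conclude, and an SAP can rename the contrast but cannot recover an RT-free comparison with usual care from these data.

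Four stronger readings are tempting, and the documents do not support them:

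- A reader might infer that the whole Phase 2 objective is lost. It is not: the randomised HIIT-versus-MICT comparison at 24 months has the same RT regime prescribed in both arms.
- For the same reason, it would be wrong to say that only the 12-week modality effect is unconfounded by RT.
- A reader might extend the criticism to the mediation models. Their exposure is called exercise training, which fairly describes the package, and their intensity question is HIIT versus MICT.
- A reader might say that RT could explain all of any difference in power. No figure in the documents bears on that share.

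The absence of RT in usual care is also a matter of prescription only. Those participants may enter pulmonary rehabilitation, and its content is not described.

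**Conclusion.** The point holds for the two contrasts with usual care. As prescribed, they compare endurance training plus about 176 sessions of RT with usual care, and their results cannot be attributed to HIIT or MICT alone. The consequence is most serious for quadriceps power, where the added component is stated to target the outcome and that outcome is enough for an efficacy claim. The conclusion rests on the prescribed regimes and the assessment schedule, not on any assumed RT effect; the share of a difference due to RT is unknown. It is separate from the non-random allocation of usual care, which affects the same contrasts by another route. The change should be made before the Phase 2 analysis is fixed.

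**What to change.** Restate the Phase 2 primary objective, and the usual-care contrasts in the analysis and reporting, as HIIT + RT versus usual care and MICT + RT versus usual care. Reserve statements about endurance modality or intensity for the randomised HIIT-versus-MICT contrasts: at 12 weeks without RT, and at 24 months on a common RT background. Add a sentence to the limitations saying that usual care has no 12-week assessment, so no RT-free comparison with it is available.

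This costs edits to the objectives, SAP and reporting text. The downside is a narrower claim against usual care. No change to training, visits or sample size is needed.

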#### Standardized phone call and letters via post

Participants with COPD will also, irrespective of the originally assigned group (HIIT or MICT) and chosen setting, receive a phone call once every 14 days. Using a standardized call protocol (see additional file 4), we will gather the necessary information to progress training intensity and information about attendance and adherence to the exercise intervention. Every third month, information about symptoms of exacerbations will also be collected via phone call (see additional file 4). Participants with COPD will also be provided with a diary where they can document their training sessions and write down additional information, e.g., change in medication. Additionally, questions on health status (CAT) and disease-specific quality of life (chronic respiratory disease questionnaire (CRQ)) will be collected every third month by sending a letter with the questionnaires via the post that will be self-administered or by a phone call.

#### Passive control group: usual care

The passive control group will receive usual care alone and a standardized phone call (see additional file 4) every 3 months including assessment of symptoms of exacerbations. Health status (CAT) and disease-specific quality of life (CRQ) will be assessed by sending a letter with the questionnaires via the post for self-administration or by a phone call. We will match the participants in the usual care group to those randomized to HIIT or MICT by age, sex, disease severity (GOLD A/B/E), educational level, and physical activity.

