#### Hospitalisations

Number of hospitalisations per participant. Time, cause, length of stay, and emergency room visits (with no hospitalization afterwards) and their cause will also be extracted. Hospitalizations and emergency room visits will be classified as respiratory or non-respiratory. Data on hospitalizations will be extracted from the participant’s medical record and, when available, cross-checked with the participant’s diary (an outcome measure only in phase 2).

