#### Exacerbations

Number of COPD exacerbations per participant (COPD only) during the trial period will be collected (an outcome measure only in phase 2).

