#### Statistical methods—outcomes

For primary and secondary outcomes with continuous data, treatment effect will be estimated by mean change-from-baseline (delta-value (Δ)) with 95% confidence intervals and the effect size (ES). The between-group effects will be analysed using analysis of covariance (ANCOVA). In the ANCOVA, baseline values, age, sex, centre, and VO_2_peak will be used as covariates. In phase 1, the primary analyses will be one model for the COPD group and one model for HC. In addition, to investigate any differential effects to the interventions between COPD and HC, a two-way ANCOVA including the Group (COPD/HC) × Intervention (supramaximal HIIT/MICT) interaction will be performed. In phase 2, there will be one model with the three arms (supramaximal HIIT, MICT, and usual care). Additional details will be provided in the SAP.

The assumptions of linearity, normality of residuals, and homogenous variance will be checked using residual plots, normal quantile plots, and histograms. Violations of linearity and normality assumptions will be dealt with by transformations of the dependent variable or non-linear modelling of the independent variables. Outliers will not be removed unless there is a methodological reason for it.

Feasibility of intervention outcomes and number of responders will be described with descriptive statistics and analysed with between group (HIIT/MICT) comparisons in both the COPD (phase 1 and 2) and HC group (phase 1).

In phase 1, hospitalization and exacerbations during the intervention will be presented descriptively. In phase 2, mortality, hospitalizations, and exacerbations will be presented with descriptive statistics and analysed using Kaplan–Meier curves and Cox proportional hazard models.

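### Exacerbations are queried every third month in all phase 2 arms, but only HIIT and MICT have extra routes by which events can be captured, and the outcome is not restricted to the common source

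*Protocol article*

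**What the plan says.** **Usual care.** Participants receive "usual care alone and a standardized phone call (see additional file 4) every 3 months including assessment of symptoms of exacerbations" (Passive control group: usual care). No diary is described for them.

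**HIIT and MICT.** Under Standardized phone call and letters via post, these participants "receive a phone call once every 14 days". The stated purpose is that "we will gather the necessary information to progress training intensity and information about attendance and adherence to the exercise intervention". The same section adds: "Every third month, information about symptoms of exacerbations will also be collected via phone call". Participants are also "provided with a diary where they can document their training sessions and write down additional information, e.g., change in medication". The phase 2 adherence section describes the diary as specific to the allocated training group, and note d to Table 3 says it is followed up in the 14-day calls. In phase 1 they train under supervision two to three times a week, and a session missed without notice prompts a call the same day.

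**Outcomes.** For exacerbations the text is: "Number of COPD exacerbations per participant (COPD only) during the trial period will be collected". Neither a source nor an event date is mentioned. Hospitalisation data, including time and cause, come from the medical record and are, "when available, cross-checked with the" participant's diary. Deaths, with time and cause, come from the medical record.

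**Analysis.** In phase 2, "mortality, hospitalizations, and exacerbations will be presented with descriptive statistics and analysed using Kaplan–Meier curves and Cox proportional hazard models" (Statistical methods—outcomes). The Trial design section states that usual care is outside the randomisation.

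**The concern.** A comparison of event counts or event times is fair only if an event has the same chance of being recorded, and of being dated in the same way, in each arm. Here the scheduled question is the same, but the surrounding contact is not. If a diary note on a medication change, or a remark in a training call, can become a recorded exacerbation, that route is open to HIIT and MICT and closed to usual care. The extra capture can run in one direction only: it raises the apparent event rate under training. It could mask a benefit of exercise or suggest a harm. Because usual care is not randomised, this comparison is already the weaker one in phase 2, and an avoidable difference in ascertainment makes it harder to interpret.

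**Working it through.** The documents give no exacerbation rate, detection probability or power for this outcome, so there is no planned figure to reproduce. The check sets the arms side by side and then illustrates what a difference in capture would do.

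**1. Ascertainment by arm**

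| Route | HIIT and MICT | Usual care |
|---|---|---|
| Exacerbation question by phone, phase 2 | every third month | every 3 months |
| Training call | every 14 days, weeks 15–102 | none |
| Diary with room for medication changes | yes | none described |
| Supervised sessions, weeks 1–12 | 2–3 per week | none |
| Medical record (hospitalisations, deaths) | yes | yes |

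Training calls: (102 − 15 + 1) / 2 = 44. Three-monthly contacts over 24 months: 24 / 3 = 8, or 7 if they follow the CAT schedule from month 6. The planned exacerbation questions in phase 2 are therefore 1:1 between arms. The asymmetry lies in the other routes.

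**2. Where those routes can enter**

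- The exacerbation outcome is not confined to the common question, so a diary entry or call remark is not excluded as an event.
- Even at the common question, an exercise participant may have a diary to consult, whereas the usual care description mentions none.
- The three-monthly question for HIIT and MICT is described under the phase 2 maintenance programme, while Table 5 marks exacerbations as collected in both phases. For weeks 1–12 the contact described for these arms is the supervised sessions.
- A Cox model needs event times. Time is requested for hospitalisations and deaths; for exacerbations only a number is.

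**3. Illustration with no true difference**

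Observed ratio = detection in exercise / detection in usual care. The detection shares are assumptions.

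- 0.80 / 0.80 = 1.00
- 0.85 / 0.80 = 1.06
- 0.90 / 0.80 = 1.13
- 0.90 / 0.70 = 1.29

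Chance of a false signal against training, for pooled exercise (n = 92) v usual care (n = 46), 24 months, no drop-out:

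- First events = 92 × (1 − exp(−2 × rate × detection in exercise)) + 46 × (1 − exp(−2 × rate × detection in usual care)).
- Power = Φ(√(events × 2/3 × 1/3) × ln(ratio) − 1.96).

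At an assumed rate of 1.0 per year and 0.90 v 0.80: events = 92 × 0.835 + 46 × 0.798 = 113.5. Then √(113.5 × 0.222) × ln 1.125 − 1.96 = 5.02 × 0.118 − 1.96 = −1.37, and Φ(−1.37) is about 8.6%.

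Over assumed rates of 0.5 to 1.5 per year, the chance is about 4–5% at 0.85 v 0.80, 7–9% at 0.90 v 0.80, and 18–27% at 0.90 v 0.70. Without any difference in detection it would be 2.5% in that direction.

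**The case against.** The strongest reply is that exacerbations are asked about at the same interval in all arms, with both descriptions pointing to the same supplementary file, and that the fortnightly calls have a different stated purpose: progression, attendance and adherence. Nothing says that they feed the event count. This stands. A reader might infer from 14 days v 3 months that exacerbations are in fact found earlier and more completely under training, with an average reporting delay of 14/2 = 7 days v 91/2, about 45 days. The documents do not support that. It treats the training call as the exacerbation question and assumes that events are dated when reported, which is stated nowhere. On the scheduled question the same formula gives about 45 days in every arm.

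It also stands that hospitalisations and deaths come from the medical record, so a claim of equal bias across all three event outcomes would go too far. The diary is only a cross-check for hospitalisations.

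Two further replies carry less weight. The absence of a diary in usual care is partly silence, but the diary is described as a training diary tied to HIIT or MICT allocation, and the hospitalisation text itself implies that not everyone has one. The section on assessments only at baseline says that medication changes are collected during the trial without naming an arm, but it gives no method for usual care.

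Finally, source and dating rules may be in the call script or the SAP, neither of which is shown. Their absence from an article is therefore not the finding. The finding is the arm-specific contact and diary, which the article does state.

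**Conclusion.** The point holds as a risk, not as a demonstrated bias. Scheduled exacerbation questioning is equal in phase 2, but the extra routes exist only in HIIT and MICT, and the outcome as worded does not shut them out. Any resulting bias would run against training in the comparison with usual care.

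Its size is unknown. The ratios of 1.06 to 1.29 and the false-signal chances of about 4% to 27% rest entirely on assumed detection shares and event rates; if the extra routes do not feed the count, the bias from them is zero. Exacerbations are mainly exposed, and hospitalisations to a lesser degree through the diary cross-check. Mortality, the three primary outcomes (measured at test visits) and HIIT v MICT (same contact in both arms) are unaffected. This is an inexpensive improvement to a secondary phase 2 comparison, not a threat to the trial's main conclusions.

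**What to change.** For the comparison with usual care, state that exacerbations and hospitalisations are counted and dated from baseline only from sources common to all three arms: the three-monthly standardised questions, with the date of each event asked, and the medical record. Ask those questions on the same schedule in every arm, so that the first 12 weeks are covered in the same way. Keep the fortnightly calls and the diary for safety and training purposes, and report events known only from them descriptively for HIIT v MICT, where ascertainment is alike.

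The cost is wording in the outcome definition, the call script and the CRF; no contacts are added. The downside is that some mild events found only through the diary or training calls drop out of the comparison with usual care. The change is best made soon, because dates not asked at the time may not be recoverable later.
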